## Abstract

**Introduction:**

The thoracic surgical procedure leads to a reduction in respiratory muscle strength. To restore it, certain strategies must be employed. Physiotherapy utilizes resources and techniques such as deep breathing stimulation, cough stimulation, use of incentive spirometers, mobilization, and ambulation. However, at times these resources and techniques may prove insufficient, and additional measures, such as Non-Invasive Ventilation (NIV), are employed Pieczkoski (2017). Non-Invasive Positive Pressure Ventilation (NPPV) has been utilized to expedite pulmonary function recovery as well as to prevent and treat postoperative pulmonary complications Nasrala 2018. NIV diminishes the risk of ventilator-associated complications due to its non-invasive nature. Consequently, NIV has been adopted to avert post-extubation complications in postoperative patients Liu 2020. The objective of this study is to conduct a randomized clinical trial and assess the efficacy of NIV in comparison to conventional physiotherapy in terms of pulmonary function among patients undergoing cardiac surgery at a selected hospital in Campina Grande, Paraíba, Brazil.

**Methods and analyses:**

This randomized, controlled, double-blind (patient and analyst) clinical trial will be conducted at Hospital João XXIII in Campina Grande, Paraíba, Brazil. Patients do not know which group they are allocated to. Those in the group that use CPAP or BIPAP will not be able to distinguish one from the other. The data analyst at the end of the collections will also be blinded. Only the health professional who will be applying the protocol cannot be blinded. The sample size, determined via sample calculation, yielded a total of 21 patients per group (63 patients). The patients will be allocated into 3 groups (CPAP group - CPAP + standard physiotherapy, BiPAP group - BiPAP + standard physiotherapy, and Control group - standard physiotherapy) in a 1:1:1 allocation ratio. The control group will receive the usual physiotherapeutic treatment as per the kinesiotherapy protocol. The treatment will be administered twice daily, starting in the ICU and progressing to the ward. In the CPAP group, nasal CPAP at 10cmH2O will be administered for 1 hour, twice daily, using an approved device. In the BiPAP group, nasal BiPAP with an IPAP of 13cmH2O and EPAP of 8cmH2O will be administered for 1 hour, twice daily, using an approved device. The NIV sessions will be conducted over the course of 5 days of hospitalization, both in the ICU and the ward. Assessments will be conducted at two time points: on day 1 preoperatively and on day 5 postoperatively. The following measures will be evaluated: pulmonary function, length of hospital stay, presence of postoperative pulmonary complications, score of the Minnesota Living with Heart Failure Questionnaire (MLHFQ) in its Portuguese version, functional capacity, the Global Perception of Change Scale, and the Functional Independence Measure (MIF). The normality of variables will be assessed using the Shapiro-Wilk test. IBM SPSS Statistics Base 25.0, using the Shapiro-Wilk test for normality and paired Student’s t-test for pre-post intervention comparison. They will use linear mixed effects models for longitudinal analysis and GLMMs to compare NIV effects over time between groups. They will employ ITT for missing data, INAR models for time dependence, fixed effects models for endogeneity, and Cohen’s d for effect sizes. Parametric model assumptions will be checked, and various models will be considered for data characteristics.

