## Material and methods

### Type of study and location of research

The study protocol was conducted following the Standard Protocol Items: Recommendations for Interventional Trials (SPIRIT) checklist. This randomized, controlled, double-blind, parallel, three-arm clinical trial will take place at the João XXIII hospital, renowned for its expertise in cardiology and particularly cardiac surgery, serving a significant portion of the state and neighboring states. The hospital carries out an average of 8 cardiac surgeries weekly. The assessment and intervention will occur in both the ICU and the general ward.

The sample size was calculated using a 95% confidence level and 80% power, while considering the outcome of pulmonary function as a reference [13, 15]. Using the calculator on the openepi.com website, we arrived at a sample size of 63 patients. Recruitment will encompass both men and women aged 18 and above who have undergone cardiac surgery. Participants will be recruited through both spontaneous demand within the service and active search within the department’s records. The sampling method will be non-probabilistic convenience sampling.

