### Professional eligibility criteria

Hospital team physiotherapists.Physiotherapy students with prior training in the research protocol.

The sample will be randomized using the website www.randomization.com into three groups: participants will be divided into three groups (CPAP group - CPAP + usual physiotherapy care, BiPAP group - BiPAP + usual physiotherapy care, and control group - usual physiotherapy care), in a 1:1:1 allocation ratio for superiority. The groups will be coded, and the allocation will be concealed in consecutively numbered sealed and opaque envelopes. This study will involve three investigators: the first will be responsible for assessments; the second will manage the protocol application; and the third will oversee randomization.

This study protocol has received approval from the research ethics committee of Universidade Estadual da Paraíba, Brazil (CAAE: 65600722.1.0000.5187), and has been submitted to Clinical Trials (NCT05966337). Patient autonomy and anonymity will be respected, ensuring the privacy of personal data in accordance with Resolution No. 510/16 of the National Health Council and the Declaration of Helsinki. Before enrolling in the study, all patients will provide informed consent.

The study protocol was conducted following the Standard Protocol Items: Recommendations for Interventional Trials (SPIRIT) checklist [16].

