#### Control group (Usual care)

Patients undergoing standard physiotherapy treatment, consisting of a kinesiotherapy protocol. Patients will receive treatment twice a day, alternating between the treatment initiated in the ICU and progressing to the general ward. Specifically, the treatment plan is divided by days and environments, taking into consideration the general characteristic that patients are discharged from the ICU on the 2nd day of the post-operative period, and Day 1 represents the first day of post-operation:

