#### Other variables

Will be collected through the analysis of the patient’s medical records, including the type of surgery, personal history, pre-operative ejection fraction, BMI, gender, and age.

*Adherence*. During the assessment and daily sessions, therapists will be instructed to raise awareness, provide guidance, and explain the purpose of the research to ensure maximum adherence to the protocol. Adherence assessment will involve direct communication between the researcher and the participating physiotherapists and students, facilitated through a dedicated messaging app group created for this purpose. Monitoring adherence will also include regular visits by the researcher during the application of the protocol treatment.

*Concomitant care*. Patients requiring extended ICU stays with the use of more advanced devices for prolonged non-invasive ventilation or even the return to invasive mechanical ventilation during the study period will be considered non-adherent from that point, and thus an intention-to-treat analysis will be employed.

*Risks and adverse effects*. Throughout the treatment, there are minimal risks of cardiac arrhythmias, decreased oxygen saturation levels, shortness of breath, bronchospasm, dizziness, syncope, hypotension or hypertension, altered heart rate, or chest pain. Throughout the entire duration, patients will be continuously monitored for vital signs.

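### The trial is called double-blind, but the control arm has no mask or sham, so patients know whether they receive NIV

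*Protocol article*

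**What the plan says.** The Abstract (Methods and analyses) describes the study as follows: "This randomized, controlled, double-blind (patient and analyst) clinical trial". It then says of patients in general, "Patients do not know which group they are allocated to", and adds "Those in the group that use CPAP or BIPAP will not be able to distinguish one from the other". On who is unmasked, it says "Only the health professional who will be applying the protocol cannot be blinded". The main text (Type of study and location of research) repeats the label without naming roles: "This randomized, controlled, double-blind, parallel, three-arm clinical trial".

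The control arm is described as "Patients undergoing standard physiotherapy treatment, consisting of a kinesiotherapy protocol" (Control group (Usual care)). A day-by-day exercise list follows there and again under Intervention protocol. The two NIV arms receive that care plus nasal CPAP or nasal BiPAP in one-hour sessions, morning and afternoon, for five days.

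Under Professional eligibility criteria, three investigators have separate tasks, of whom "the first will be responsible for assessments". Whether that person is blinded is not stated. The Adherence paragraph (Other variables) tells therapists to "provide guidance, and explain the purpose of the research to ensure maximum adherence to the protocol".

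**The concern.** The claim of patient blinding covers all three arms, but the treatments in two of them are visibly different from the third. If patients can tell NIV from control, the label is wrong for the comparison the trial was set up to make.

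The outcomes make this matter. FEV1 and FVC belong to a primary outcome and depend on patient effort and on how the test is coached. TUG is a timed performance. MLHFQ and the perception-of-change scale are the patient's own report. Expectation or coaching can move each of them without any effect on the lungs. Blinding the analyst does not help, because the bias enters at measurement. A reader who trusts the label would rate the risk of bias too low.

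**Working it through.** The main check is a comparison of the article's own statements.

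**1. What each arm experiences**

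| Arm | Content | Device on the patient |
|---|---|---|
| Control | Kinesiotherapy (Control group (Usual care); Intervention protocol) | None in either description |
| CPAP | Control care plus nasal CPAP, 1 hour, twice daily, 5 days | Yes: 2 × 5 = 10 one-hour sessions |
| BiPAP | Control care plus nasal BiPAP, 1 hour, twice daily, 5 days | Yes: 2 × 5 = 10 one-hour sessions |

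The control programme is set out in full twice, and neither version includes a mask, a sham pressure or an inactive device.

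**2. Can patients tell?** The Inclusion criteria require patients to be awake, orientated and able to cooperate. Such a patient knows whether a nasal device was used for ten hours over five days.

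**3. Which contrasts can be masked?** Three arms give three pairwise contrasts.

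| Contrast | Masked to patients? |
|---|---|
| CPAP vs BiPAP | Claimed in the Abstract; plausible |
| CPAP vs control | No |
| BiPAP vs control | No |

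The Primary objective compares the NIV modalities with conventional physiotherapy, so it concerns the two unmasked contrasts.

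**4. Which outcomes are exposed?** FEV1 and FVC (Pulmonary function), TUG (Funcional capacity), MLHFQ (Quality of life) and the perception-of-change scale. Blood gases are less exposed. Length of stay, the other primary outcome, is neither effort-dependent nor self-reported, although the treating staff are unmasked.

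**5. Who remains blinded?** The named roles are patient and analyst. Without patient masking against control, only the analyst is left.

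**6. Size, as an illustration only.** The documents give no estimate of the bias, so the shifts below are assumptions. Take n = 21 per arm (Abstract; 3 × 21 = 63), a two-sided 5% t-test, no true effect, and a systematic shift of b standard deviations between an NIV arm and control. The test has 2 × 21 − 2 = 40 degrees of freedom, and the noncentrality is b × √(21/2) = 3.24b. The chance of a significant result is the two-sided rejection probability of the noncentral t:

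| Assumed shift b (SD) | Noncentrality | Chance of p ≤ 0.05 with no true effect |
|---|---|---|
| 0 | 0 | 5% |
| 0.1 | 0.32 | 6.2% |
| 0.2 | 0.65 | 9.7% |
| 0.3 | 0.97 | 15.8% |
| 0.5 | 1.62 | 35.3% |

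The finding does not depend on these figures.

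**The case against.** The strongest reply accepts that the sentence is too broad for NIV against control and argues that this is a labelling slip. An open usual-care comparator is a legitimate design. The Abstract defines its label, and the sentence after the disputed one mentions only CPAP against BiPAP, so a careful reader can see the limit. Saying that only the treating professional cannot be blinded implies that the assessor can be, and a condensed article may leave the masking procedure to the full protocol. The consent form is not shown, so what patients learn about the other arms is unknown, and the Adherence sentence does not say to whom the purpose is explained. Spirometry requires at least three manoeuvres agreeing within 5%, which limits variation in effort. The Protocol modifications section rules out changes after registration.

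Some of this stands:

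- The design need not change, and no sham is asked for.
- The consent and adherence passages are only supporting evidence. The visible device is enough.
- The text on the assessor is incomplete and does not rule out masking.

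The rest does not remove the point:

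- A condensed article may omit detail, but here it makes a positive statement that its own arm descriptions contradict.
- Saying that only one role cannot be blinded implies at most that the assessor could be. It does not say that the assessor will be.
- Agreement between manoeuvres in one session does not prevent a consistent difference in effort or coaching between arms.
- A rule against modifications is no reason to leave an incorrect description uncorrected.

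**Conclusion.** The concern holds. As written, the statement that patients do not know their group is wrong for both NIV-versus-control contrasts, two of the three possible, and those are the contrasts in the primary objective. It affects FEV1, FVC, TUG, MLHFQ and perception of change. This rests on one inference: that no sham exists, because two full descriptions of the control programme contain none.

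The missing statement on assessor masking is a secondary point, but it matters in practice because it is the protection still available for the performance tests. The size of any bias cannot be derived from the documents. This must be fixed, because readers will rely on the claim when judging an effort-dependent primary outcome.

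**What to change.** 1. In the Abstract, delete the general sentence on patient blinding and replace the label with: *outcome assessor and analyst blinded; patients masked only between CPAP and BiPAP; open to patients for NIV versus control*. Change the label under Type of study and location of research to match.
2. Make the assessor part of that wording true before printing it. State that the first investigator performs the postoperative spirometry, TUG and MIF without access to allocation and away from NIV equipment, asks patients not to disclose their treatment, and records whether the blind was broken. If this cannot be done, say that the assessor is not blinded.
3. Label NIV-versus-control results on MLHFQ and perception of change as open-label, since assessor masking cannot protect self-report.

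The cost is a few lines of text and a short instruction. The assessor is already a separate role, so extra staff should not be needed. The sponsor should confirm that whoever does the postoperative assessment has no treatment duties, because students may deliver the intervention and the Consent or assent section also mentions students at the initial assessment. The change should be recorded openly as a correction, given the Protocol modifications section. The blinding claim becomes less favourable, but it will be accurate.

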#### Perception of change

The GPCS is a self-report tool that assesses an individual’s perception of change in a specific domain. It uses Likert-scale items ranging from "a very great deal worse/less" to "a very great deal better/more" to capture subjective information about perceived change [20].

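### Patient blinding is claimed for all three arms, but the arms as described allow it at most between CPAP and BiPAP, not for NIV versus conventional physiotherapy

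*Protocol article*

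**What the plan says.** The abstract (Methods and analyses) makes four statements on blinding:

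- the label: "This randomized, controlled, double-blind (patient and analyst) clinical trial will be conducted at Hospital João XXIII";
- for patients: "Patients do not know which group they are allocated to";
- the support offered: "Those in the group that use CPAP or BIPAP will not be able to distinguish one from the other";
- the exception: "Only the health professional who will be applying the protocol cannot be blinded".

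The Methods section on type of study and location repeats the label without saying who is blinded: "This randomized, controlled, double-blind, parallel, three-arm clinical trial".

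The control arm is introduced under Control group (Usual care) as "Patients undergoing standard physiotherapy treatment, consisting of a kinesiotherapy protocol". It is then listed day by day, once under Interventions and again under Intervention protocol. The lists contain breathing and limb exercises, cough stimulation, walking and, on Day 2, a cycle ergometer and an incentive spirometer. The CPAP and BiPAP arms receive that same care plus a nasal pressure device for 1 hour, morning and afternoon, for 5 days.

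The primary objective compares NIV, in its two modalities, with conventional physiotherapy.

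**The concern.** The claim about patients covers every arm, but the reason given for it concerns only the two device arms. A conscious patient knows whether a pressurised nasal mask is being worn. If so, the patient is unblinded in the comparison that the trial exists to make.

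This matters because several outcomes come from the patient. MLHFQ is a questionnaire, and the protocol describes the change scale in these words: "The GPCS is a self-report tool". Spirometry and TUG need the patient's effort. Patients who know that they received the additional treatment may rate themselves better, or try harder, with no effect on the lung. A report that carries the double-blind label would tell readers that such differences are protected from this bias.

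**Working it through.** The main check sets the blinding statements against the arm descriptions.

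**Step 1. Device exposure by arm** (intervention group descriptions; 2 sessions a day for 5 days).

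| Arm | NIV sessions of 1 hour | Mask or sham |
|---|---|---|
| CPAP | 2 × 5 = 10 | nasal device |
| BiPAP | 2 × 5 = 10 | nasal device |
| Control | 0 | none described |

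**Step 2. Which comparisons can be masked for the patient.**

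| Comparison | Visible difference | Patient masking possible? |
|---|---|---|
| CPAP versus BiPAP | pressure pattern only | at most here, as the abstract asserts |
| CPAP versus control | 10 sessions versus 0 | no |
| BiPAP versus control | 10 sessions versus 0 | no |

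The inclusion criteria require patients to be conscious, oriented and cooperative, so sedation does not hide the difference. The last two rows are the primary objective.

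**Step 3. What an expectation effect could do (illustration).** The plan gives no figure to reproduce here. The inputs are:

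- n = 21 per arm (abstract);
- significance level 5% (Statistical analysis), taken as two-sided;
- an assumed shift d, in SD units, in a self-rating with no true treatment effect. This is an assumption, and the documents give nothing from which to estimate it.

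For one two-sample t-test, df = 2 × 21 − 2 = 40 and the critical value is 2.021. The non-centrality is d × √(21/2) = d × 3.240. The rejection probability is P(|T| > 2.021) for the non-central t with 40 df.

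| Assumed shift d | Non-centrality | False-positive rate |
|---|---|---|
| 0 | 0 | 5.0% |
| 0.1 | 0.324 | 6.2% |
| 0.2 | 0.648 | 9.7% |
| 0.3 | 0.972 | 15.8% |
| 0.5 | 1.620 | 35.3% |

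The plan specifies mixed models for the between-group comparison, so the t-test stands in for one NIV-versus-control contrast on one self-rated outcome. It is not a reproduction of the planned analysis.

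**The case against.** An unblinded usual-care control is a common design and is not an error in itself. That is right, and no sham is asked for here. The error is the statement that patients are blinded.

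The primary outcomes are less exposed than the label problem suggests. Length of stay is a count of days. Spirometry requires at least three tests with less than 5% variation and takes the highest value, which limits erratic effort but does not remove every effect of motivation. The clearly exposed outcomes, MLHFQ and GPCS, are secondary. This stands and limits the reach of the point.

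Four stronger readings are tempting, and the document does not support them.

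- *Therapists tell control patients that the trial is about NIV.* Under Adherence, "therapists will be instructed to raise awareness, provide guidance, and explain the purpose of the research to ensure maximum adherence to the protocol". This happens during the assessment and daily sessions, but the text does not say what purpose is described, or that any expectation about an arm is voiced. The consent form is not shown. The point therefore rests on the visible device alone.
- *Control patients receive no equipment at all.* They use a cycle ergometer and an incentive spirometer on Day 2. Neither imitates NIV, so the accurate wording is no NIV device, mask or sham.
- *The Methods section names the patient as blinded.* It says only double-blind; the parties are named in the abstract.
- *The trial's error rate is 10% to 35%.* Those figures depend on an assumed shift in a self-rating. At 0.1 SD the rate is about 6%, and nothing is quantified for either primary outcome.

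The section on protocol modifications rules out changes after publication in the trials database. Correcting a misdescribed feature alters no procedure, and that rule is no reason to leave an untrue statement in place.

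**Conclusion.** The point holds. The plan states that patients are blinded across all arms and that only the treating professional is not. Its own arm descriptions contradict this for two of the three pairwise comparisons, and those two are the primary objective. This conclusion needs no numerical assumption. It requires only that a conscious patient notices whether a nasal pressure device is applied ten times.

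The consequence is greatest for NIV versus control on MLHFQ and GPCS, smaller for spirometry and TUG, and does not arise through self-report for length of stay. Its size is unknown; the range of about 6% to 35% is conditional on an assumed shift of 0.1 to 0.5 SD. The statement that CPAP and BiPAP users cannot tell the modalities apart is asserted without further support, but nothing in the document contradicts it. Analyst blinding is unaffected.

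**What to change.** In the abstract, remove the patient-and-analyst double-blind label together with the sentences "Patients do not know which group they are allocated to" and "Only the health professional who will be applying the protocol cannot be blinded". The last must go too, because it would contradict the correction. Replace them with: *patients in the NIV arms are masked to modality (CPAP or BiPAP) only; patients and treating professionals are not blinded for NIV versus control; the data analyst is blinded.*

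Qualify the double-blind label in the Methods section and in the registry entry to match. State that NIV-versus-control results on MLHFQ and GPCS will be reported as open-label self-report.

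Optionally, use one neutral script in all arms for the explanation of the research described under Adherence.

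The cost is wording in the protocol and registry, plus a short script if that option is taken. Treatment, sample size, staffing and analysis do not change. The drawback is a less favourable blinding label.
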